## Abstract

**Background::**

Coronary heart disease is a serious cardiovascular disease. There is coronary atherosclerosis, resulting in lumen stenosis, blockage, and then the symptoms of insufficient blood supply and hypoxia in the myocardium. Chronic heart failure is a kind of syndrome with abnormal ventricular filling and ejection function, which is the final stage of the development of coronary heart disease. At present, the treatment plan of Western medicine can significantly reduce the hospitalization rate, but it is still not satisfactory for the prognosis and mortality of patients. Shenfu injection has advantages in the treatment of heart failure in patients with coronary heart disease, but there is a lack of standard clinical studies to verify it, so the purpose of this randomized controlled study is to evaluate the efficacy and safety of Shenfu injection combined with sodium nitroprusside in the treatment of chronic heart failure in patients with coronary heart disease.

**Methods::**

This is a prospective randomized controlled trial to study the efficacy and safety of Shenfu injection combined with sodium nitroprusside in the treatment of chronic heart failure in patients with coronary heart disease. The patients will be randomly divided into a treatment group and the control group according to 1:1, in which the treatment group is treated with Shenfu injection combined with sodium nitroprusside, and the control group is treated with sodium nitroprusside alone. Both groups will be treated with standard treatment for 7 days and followed up for 30 days to pay attention to their efficacy and safety indexes. The observation indexes include TCM syndrome score, N-terminal pro-brain natriuretic peptide, left ventricular ejection fraction, brain natriuretic peptide, left ventricular end-systolic diameter, left ventricular end-diastolic diameter, stroke volume, adverse reactions and so on. We will use SPSS 25.0 software for data analysis.

**Discussion::**

This study will evaluate the efficacy and safety of Shenfu injection combined with sodium nitroprusside in the treatment of chronic heart failure in patients with coronary heart disease. The results of this experiment will provide a clinical basis for Shenfu injection combined with sodium nitroprusside in the treatment of chronic heart failure in coronary heart disease.

**Trial registration::**

DOI 10.17605/OSF.IO/4KNG3

## Introduction

1

Chronic heart failure is characterized by abnormal cardiac structure and function, which lead to the decrease of ventricular ejection fraction and ventricular filling, which cannot meet the metabolic needs of body tissue. It is a critical cardiac disease and the main cause of death in heart patients.^[1]^ The incidence of heart failure in China is 0.9%, which is higher in women than in men, higher in the north than in the south, and higher in cities than in rural areas.^[2]^ The European Society of Cardiology found that there are more than 15 million patients with heart failure for every 1 billion people, with a total prevalence rate of 2% to 3% in the general population and 10% to 20% in people aged 70 to 80.^[3]^

Sodium nitroprusside has a certain value in improving the prognosis of patients with chronic heart failure.^[4]^ Sodium nitroprusside is a vasoactive drug, which can effectively dilate small arteries and veins, selectively relax vascular smooth muscle and reduce peripheral vascular resistance, temporarily change hemodynamic variables, reduce blood pressure, relieve cardiac load, and increase cardiac output.^[5]^ However, long-term use of nitric oxide donor sodium nitroprusside can lead to outflow tissue damage through protein nitrification, resulting in an increase in intraocular pressure, and drug withdrawal cannot recover.^[6]^

Traditional Chinese medicine in the treatment of chronic heart failure in patients with coronary heart disease can effectively alleviate the symptoms of heart failure and improve the quality of life of patients.^[7,8]^ According to the theory of traditional Chinese medicine, the main pathogenesis of chronic heart failure is yang-deficiency of heart and kidney.^[9]^ Shenfu injection is made from ginseng and aconite extract. Modern medical research has found that Shenfu injection can reduce peripheral vascular resistance, improve microcirculation,^[10]^ protect cardiomyocytes,^[11]^ and protect vascular endothelium.^[12]^ At the same time, Shenfu injection has small clinical adverse reactions and a safe wide range of dose. Therefore, we intend to use this randomized controlled trial to evaluate the efficacy and safety of Shenfu injection combined with sodium nitroprusside in the treatment of chronic heart failure in patients with coronary heart disease.

## Materials and methods

2

### Study design

2.1

This is a prospective randomized controlled trial to study the efficacy and safety of Shenfu injection combined with sodium nitroprusside in the treatment of coronary heart disease with chronic heart failure. This trail will follow the comprehensive test reporting standards, and the flow chart is shown in Fig. 1.

**Figure 1 F1:**
[figure not shown]
Flow diagram.

### Ethics and registration

2.2

This research scheme is in line with the Helsinki Declaration and approved by the Clinical Research Ethics Committee of our hospital. This research scheme has been registered on OSF (registration number: DOI 10.17605/OSF.IO/4KNG3). Before being randomly divided into groups, all patients need to sign a written informed consent form, and they are free to choose whether to continue the trial at any time.

### Patients

2.3

Inclusion criteria: meet the diagnostic criteria of coronary heart disease, refer to the 2017 Chinese guidelines for Prevention and treatment of Cardiovascular Diseases; meet the diagnostic criteria of chronic heart failure,^[13]^ Doppler ultrasound indicates that the left ventricular ejection fraction is less than 50%,^[14]^ and the condition was in stable stage; age 40 to 79 years old; all patients signed consent.

Exclusion criteria: patients with other serious cardiovascular diseases; patients with other serious diseases such as malignant tumors; patients with severe mental illness; patients who are allergic to or have contraindications to medication in this study; unable to understand the study plan or unwilling to participate after explanation.

### Sample size calculation

2.4

This study was a pilot clinical trial. According to the analysis and calculation of the related literature published in the past 10 years, the therapeutic efficiency of Western medicine is 72.3%, and the effective rate of traditional Chinese medicine combined with Western medicine is 92.1%. Using the sample size estimation formula compared with multiple sample rates, set the significance test level α = 0.05, then μ_α_ = 1.96, 1−β = 0.9, μ_β_ = 1.28. δ = π_1_−π_2_ sample size estimation formula for comparison of 2 sample rates:$$N_{1}=N_{2}={\left(\frac{\mu_{\alpha }+\mu_{\beta }}{\delta }\right)}^{2}[\pi_{1}(1-\pi_{1})+\pi_{2}(1-\pi_{2})]$$

The sample size of each group is calculated to be 73. Considering shedding and other factors, the expansion is about 20%, and it is calculated that 182 patients need to be included. According to the simple randomized method, the patients included in the study are divided into control group (n = 91) and the observation group (n = 91).

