### Evaluation criteria and judgment of curative effect

2.6

1.Main outcome indicators: TCM syndrome score (refer to the guiding principles of Clinical Research of New drugs of traditional Chinese Medicine^[15]^), N-terminal pro-brain natriuretic peptide (NT-pro BNP), left ventricular ejection fraction, brain natriuretic peptide (BNP).2.Secondary outcome indicators: stroke volume (SV), left ventricular end-systolic diameter, left ventricular end-diastolic diameter.3.Adverse reactions: including abnormal liver function and uncomfortable symptoms (such as dizziness, nausea, etc) during treatment.

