The purpose of this randomized controlled trial is to verify that Shenfu injection can significantly improve the clinical symptoms and cardiac function in patients with chronic heart failure in patients with coronary heart disease. Since there is no standard clinical study to evaluate the efficacy of Shenfu injection combined with sodium nitroprusside in patients with heart failure of coronary heart disease, we intend to evaluate its efficacy and safety through prospective randomized controlled trials.

This study also has some limitations: due to the short planned follow-up time, we are unable to understand the impact of long-term results, so we may extend the follow-up time if necessary. And due to the influence of treatment, this study cannot achieve strict double-blindness, which may affect the results to a certain extent.

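### The sample size and its 90% power rest on an effective rate that the plan neither defines nor lists as an outcome, so that power is unsupported for the four listed main outcomes

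*Protocol article*

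**What the plan says.** Section 2.4 (Sample size calculation) of the protocol article takes two rates from published literature: "the therapeutic efficiency of Western medicine is 72.3%, and the effective rate of traditional Chinese medicine combined with Western medicine is 92.1" per cent. It instructs the reader to "set the significance test level α = 0.05", with quantiles 1.96 and 1.28 (90% power), and applies a "sample size estimation formula for comparison of 2 sample rates". The result is "The sample size of each group is calculated to be 73", raised by about 20% for loss to 182 patients, 91 per arm.

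Section 2.6 (Evaluation criteria and judgment of curative effect) lists the main outcomes as the TCM syndrome score followed by "N-terminal pro-brain natriuretic peptide (NT-pro BNP), left ventricular ejection fraction, brain natriuretic peptide (BNP"). The secondary outcomes are stroke volume and two left ventricular diameters, and the only other item is adverse reactions. No effective rate or responder outcome appears there, nor among the observation indexes named in the abstract.

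Section 2.8 assigns t tests, or rank sum tests where the data are not normal, to measurement data and a chi-square test to counting data. It does not mention an effective rate.

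**The concern.** A power statement belongs to a particular outcome, effect size and test. Here the outcome behind the calculation is a yes/no rate compared as two proportions, while the outcomes named as main are four scale measures compared by t or rank sum test. The document gives no expected difference or SD for any of the four, so the 90% cannot be carried over to them.

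The two rates are also labelled only as Western medicine and combined Chinese and Western medicine. Section 2.4 does not tie them to nitroprusside with or without Shenfu, which is the comparison in section 2.5.

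What is at stake is how the results will be read. The Discussion sets out to "verify that Shenfu injection can significantly improve the clinical symptoms and cardiac function". A non-significant result on, say, NT-proBNP or LVEF could be taken as coming from a trial with 90% power for that outcome, and nothing in the document supports this.

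**Working it through.** **Inputs from section 2.4.** Rates 0.723 and 0.921, difference 0.198; quantiles 1.96 (two-sided 0.05) and 1.28 (90% power); loss about 20%.

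**Step 1: reproduce the plan's figure.** The plan's formula is n per arm = ((1.96 + 1.28)/δ)² × [π₁(1−π₁) + π₂(1−π₂)].
- (3.24/0.198)² = 267.77
- 0.723 × 0.277 + 0.921 × 0.079 = 0.2003 + 0.0728 = 0.2730
- 267.77 × 0.2730 = 73.1 per arm, matching the stated 73
- 73/0.80 = 91.25 per arm, or 182.5 in total, matching 182 as 91 per arm

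The exact power of the chi-square test for these two rates at 73 per arm is 90.3%. The calculation is sound for the quantity it uses.

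**Step 2: look for that quantity among the outcomes.** The items in section 2.6 are one score, two natriuretic peptides, LVEF, stroke volume, two diameters and adverse reactions. None is an effective rate, and no threshold is given that would turn any of them into one.

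**Step 3: what 73 per arm offers for a scale outcome.** The document supplies no difference or SD, so the standardised differences below are assumptions made for illustration.

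The detectable difference at 90% power is approximately (1.96 + 1.28) × √(2/73) = 3.24 × 0.1655 = 0.536 SD. Using the t distribution it is 0.54 SD. If all 91 per arm were evaluable it would be 0.48 SD.

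Power of a two-sample t test, two-sided 0.05, 73 evaluable per arm:

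| Assumed difference (SD) | Power |
|---|---|
| 0.3 | 44% |
| 0.4 | 67% |
| 0.5 | 85% |
| 0.54 | 90% |
| 0.6 | 95% |

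Over this range power runs from under one half to well above the stated 90%, and the document gives no means of saying which row applies to which outcome.

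**The case against.** **The rate may be a dichotomised TCM syndrome score.** This is the strongest defence. Section 2.6 has judgment of curative effect in its heading, lists the score first and refers it to guiding principles that are not reproduced; section 2.8 provides a chi-square test for counting data. If the rate came from cutting a roughly normal score with equal variances (an assumption), 72.3% against 92.1% would correspond to a shift of 1.41 − 0.59 = 0.82 SD, and a t test on the score with 73 per arm would have over 99% power. A condensed article might simply have left out the responder rule. This makes an innocent explanation plausible for one outcome. It does not remove the mismatch: section 2.6 names the score itself, without a responder category, and the other three main outcomes would still have no power basis.

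**The study is called a pilot.** Section 2.4 uses that label, and no passage says how a non-significant result will be interpreted, so the risk of misreading is an inference. But the same section makes a formal 90% power calculation, and that calculation should refer to a listed outcome.

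**A stronger reading is tempting.** A reader might infer that the trial lacks adequate power for its main outcomes. The document does not support this. With no difference or SD stated, power is unknown, and it reaches 90% or more for any true difference of about 0.54 SD or larger. Nor should the case be enlarged by dividing alpha across the four outcomes, since the plan makes no such division, or by quoting a gain from baseline adjustment, since section 2.8 plans none.

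**Conclusion.** The point holds as a conflict between two stated parts of the plan. The 73 per arm, the total of 182 and the 90% power are derived for an effective rate that section 2.6 neither defines nor lists, so the stated power is unsupported for all four listed main outcomes. Because the article sets out both the calculation and the outcome list, this is not merely a detail left to another document.

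The arithmetic is not at fault, and inadequate power has not been shown. The 0.54 SD figure assumes a two-sample t test, two-sided 0.05 and 73 evaluable patients per arm; the power values at other differences rest on assumed effect sizes.

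**What to change.** Keep 182 patients and make sections 2.4 and 2.6 agree, in one of two ways.

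(a) If the effective rate is the intended primary outcome, list it in section 2.6 as the single primary outcome with its responder definition, test it by chi-square, and state in section 2.4 that the 90% power applies to it alone. This follows most directly from the existing calculation.

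(b) Otherwise, name one listed main outcome as primary, remove the 72.3% and 92.1% basis, and restate section 2.4 along these lines: 73 evaluable patients per arm give 90% power at two-sided 0.05 to detect a difference of 0.54 SD. The sponsor should then say whether a difference of that size is plausible and worth detecting for the chosen outcome.

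The cost is rewording only, with no extra patients. Under (b), the stated power becomes less favourable for modest effects: 67% at 0.4 SD and 44% at 0.3 SD.

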### Study design

2.5

In this study, through prehospital recruitment, in-hospital inpatients to screen patients who meet the criteria, patients and their families approve the study program and sign the informed consent form. The patients will be randomly assigned to the treatment group and the control group. Among them, the treatment group will receive Shenfu injection (Shenfu injection 40 mL injection + 5% GS 250 mL injection, ivgtt, QD) combined with intravenous drip of sodium nitroprusside (sodium nitroprusside 3 μ g / kg/min), while the control group will only receive intravenous drip of sodium nitroprusside. Patients in both groups will receive the same routine care and drug treatment, such as angiotensin converting enzyme inhibitor/angiotensin II receptor blocker, beta blocker, diuretic, etc. If necessary, the attending physician can adjust the program according to the patient's condition, and all interventions will be recorded in detail for final result analysis. We will set up a special drug manager, and the nurse will be responsible for preparing the medicine and preparing the solution. Therefore, the study is not blind to nurses, but to researchers, patients, and statisticians. All patients will receive an intravenous injection once a week. The health status of each patient is evaluated before and after treatment, including efficacy and safety indicators, and all patients are followed up by telephone for 30 days. Follow-up included cardiovascular events and rehospitalization.

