### Data collection and management

2.7

The data are collected according to the evaluation criteria before the beginning of treatment, 72 hours after the treatment and at the end of treatment. Thirty days after the end of treatment, each patient is followed up by outpatient or telephone. The reasons for the loss of follow-up cannot be collected. All data will be collected jointly by 1 or 2 assistants. Personal information about potential participants and registered participants will be collected, shared, and stored in a separate storeroom to protect before, during, and after confidentiality. The access to the database is limited to the researchers of this research group.

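### Section 2.5 says patients and researchers are blinded, but only one arm gets an extra, visible infusion, so the claim is wrong for patients and bedside staff

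*Protocol article*

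**What the plan says.** Protocol article, section 2.5, on blinding: "Therefore, the study is not blind to nurses, but to researchers, patients, and statisticians". The sentence is drawn as a consequence of the one before it: "We will set up a special drug manager, and the nurse will be responsible for preparing the medicine and preparing the solution".

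The same section describes the arms. The treatment group receives "Shenfu injection 40 mL injection + 5% GS 250 mL injection, ivgtt, QD" together with the nitroprusside drip, "while the control group will only receive intravenous drip of sodium nitroprusside". The Methods paragraph of the abstract agrees: "the control group is treated with sodium nitroprusside alone".

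The limitations paragraph of the Discussion (section 3) says: "due to the influence of treatment, this study cannot achieve strict double-blindness, which may affect the results to a certain extent".

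Section 2.6 opens its list with "Main outcome indicators: TCM syndrome score" and then names NT-proBNP, left ventricular ejection fraction and BNP. It also lists adverse reactions, including felt symptoms such as dizziness and nausea. On who gathers the data, section 2.7 says: "All data will be collected jointly by 1 or 2 assistants". It does not say whether those assistants know the allocation.

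**The concern.** Blinding of patients requires that the two arms look alike to the patient. Here they differ by a whole infusion. Under section 2.5, patients and their families approve the study plan before entry. If they know what it compares, a patient can tell the arm from whether the Shenfu bag is hung, and so can anyone at the bedside. Handing preparation to a nurse protects against seeing the preparation, not against seeing the infusion.

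Two things are at stake. First, the trial report would carry a statement about patient blinding that its own methods contradict. Second, a group difference in an outcome that depends on what patients say could not be separated from expectation. This applies to the felt adverse symptoms. It appears to apply to the TCM syndrome score as well, given its name and the Discussion's stated aim of showing improved clinical symptoms.

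**Working it through.** **Step 1. The statements side by side.**

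| Place | Content | Consistent with blinded patients? |
|---|---|---|
| 2.5, blinding sentence | Nurses unblinded; researchers, patients, statisticians blinded | This is the claim |
| 2.5, preparation | Drug manager; nurse prepares the solution | Hides preparation only |
| 2.5, treatment arm | Extra infusion, 40 + 250 = 290 mL, plus nitroprusside | No, unless masked or matched |
| 2.5, control arm | Nitroprusside drip only | No: nothing matches the extra bag |
| Abstract, Methods | Control: nitroprusside alone | No: same description |
| 3, Discussion | Strict double-blinding not achievable | Points the same way, more softly |

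The control arm is described positively as having one drip. A matching infusion is thus excluded by the wording, not merely left out by a condensed article. The claim fails for patients and for anyone who sees the infusion. Nothing contradicts the blinding of statisticians. For laboratory staff and the echocardiography reader the article says nothing specific, and blinding them is feasible.

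**Step 2. Sample sizes used in the illustration.** Section 2.4 gives rates of 72.3% and 92.1%, multipliers 1.96 and 1.28, and δ = 0.921 − 0.723 = 0.198. Its own formula gives

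((1.96 + 1.28)/0.198)² × [0.723 × 0.277 + 0.921 × 0.079] = 267.77 × 0.27303 = 73.11,

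which reproduces the stated 73 per group. Allowing for about 20% loss, 73/0.8 = 91.25, against the stated 91 per arm (182 in total). These figures do not bear on blinding; they only supply n.

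**Step 3. What an expectation bias could do (illustration only).** The documents give neither an SD for the score nor a size for the bias, so the bias b is an assumption, shown over a range in SD units. Assume no true drug effect, a score analysed as continuous, and the two-group comparison of section 2.8 at two-sided 0.05, in its normal approximation. With SE = √(2/n),

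P(P<0.05) = Φ(b/SE − 1.96) + Φ(−b/SE − 1.96).

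For n = 73, SE = √(2/73) = 0.1655. For n = 91, SE = √(2/91) = 0.1482. Example: b = 0.1, n = 73 gives b/SE = 0.604, and Φ(−1.356) + Φ(−2.564) = 0.088 + 0.005 = 0.093.

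| Assumed bias (SD) | 73 per arm | 91 per arm |
|---|---|---|
| 0.1 | 9% | 10% |
| 0.2 | 23% | 27% |
| 0.3 | 44% | 53% |
| 0.4 | 68% | 77% |
| 0.5 | 86% | 92% |

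With no bias the figure is 5%. A larger trial makes the problem worse, because bias does not shrink with n.

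**The case against.** The best defence is that sections 2.5 and 3 can be read together. Section 2.5 already says nurses are unblinded, and the Discussion says only that *strict* double-blinding is out of reach and may affect the results. On that reading the plan describes partial blinding and discloses the limit. This partly stands. The Discussion does disclose a weakness, and it should not be read as admitting that blinding fails altogether. It does not rescue the claim about patients, because the conflict lies inside section 2.5, between the blinding sentence and the arm description.

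Several stronger readings are tempting, but the documents do not support them:

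- *The TCM score is the primary outcome, so the whole trial falls.* Section 2.6 names four main outcomes and states no ranking. Two of them, NT-proBNP and BNP, are laboratory assays. The article describes neither the content of the score nor its rater, so its symptom-based nature is an inference.
- *The extra fluid itself shifts natriuretic peptides or ventricular diameters.* No passage says so. The total volume is not settled either: section 2.5 writes the Shenfu infusion as once daily, yet also says all patients receive an intravenous injection once a week. Those statements need reconciling in their own right.
- *NT-proBNP must become the sole primary outcome.* This does not follow from a wrong blinding statement, and it would depart from the response rates on which section 2.4 sizes the trial.
- *Treating physicians will skew co-treatment.* They may adjust the program, but section 2.5 does not say whether they count among the blinded researchers, and it requires interventions to be recorded in detail. Unequal co-treatment is possible but not shown.
- *One assistant can simply be kept away from infusions to score symptoms.* Section 2.7 allows for only one assistant, and a separate rater would not remove expectation from what patients report.

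**Conclusion.** The claim of patient and bedside blinding is wrong as written. This follows from the article's own description of the arms and needs no outside assumption beyond the extra infusion being visible when no masking is described. It extends to researchers as far as they see patients during infusion; the term is not defined. Statistician blinding is not contradicted.

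The consequence is exposure to expectation bias in the felt adverse symptoms and, on the inference that it is symptom-based, in the TCM syndrome score. The size of that bias is unknown. Over an assumed 0.1 to 0.5 SD, the chance of a significant result with no drug effect runs from about 9% to 86% at 73 per arm and from 10% to 92% at 91 per arm. The width of that range reflects the assumption. No single value from the table should be quoted as the trial's error rate.

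**What to change.** Replace the blinding sentence in section 2.5 with wording such as: *open-label for patients, nurses and treating physicians; laboratory staff, the echocardiography reader and the statistician work from coded data without allocation*. Bring the limitation in the Discussion into line with it. Report the TCM syndrome score and subjective adverse reactions as unblinded outcomes, and do not let conclusions on efficacy rest on the TCM score alone. State who rates the score and that the rating is unblinded.

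The cost is small: a rewritten sentence, a matching line in the Discussion, and coded labels on samples and echocardiography files. The coding must actually be done for the second half of the new sentence to be true. The downside is that the trial loses its blinded label. The outcomes and the sample size can stay as they are.

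If the sponsor wishes to keep the claim of patient blinding, the clinical team must reconcile the arm description with the blinding sentence; the two cannot both stand as they are.

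### Section 2.5 contradicts itself on infusion frequency: Shenfu is once daily in the drug specification, but a later sentence gives every patient one intravenous injection a week

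*Protocol article*

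**What the plan says.** Section 2.5 gives the experimental regimen as "Shenfu injection 40 mL injection + 5% GS 250 mL injection, ivgtt, QD", added to "intravenous drip of sodium nitroprusside (sodium nitroprusside 3 μ g / kg/min". For the comparator, it says "the control group will only receive intravenous drip of sodium nitroprusside". Further down the same paragraph, after the arrangements for drug preparation and blinding, it says "All patients will receive an intravenous injection once a week".

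The only number of treatment days is in the Abstract, under Methods: "Both groups will be treated with standard treatment for 7 days and followed up for 30 days". Sections 2.1 to 2.8 do not repeat it.

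Section 2.7 sets data collection at "before the beginning of treatment, 72 hours after the treatment and at the end of treatment", and then adds "Thirty days after the end of treatment, each patient is followed up by outpatient or telephone".

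**The concern.** A once-daily Shenfu infusion and a weekly injection for all patients cannot both describe how Shenfu is given. The two statements stand in one paragraph, and both are operative text. The weekly sentence does not say which injection it means. Because it covers all patients, it also reaches the controls, who get no Shenfu. Taken literally, it would then also set a frequency for nitroprusside, for which section 2.5 otherwise gives only a rate.

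Shenfu is the only planned difference between the arms. Its frequency therefore defines the treatment contrast, and it decides what counts as adherence or as a protocol deviation. Nurses prepare the solutions, so they are among those who need one unambiguous schedule. Two intravenous drugs are involved, so the written frequency should not be open to two readings.

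**Working it through.** **The statements side by side**

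| Source | Drug named | Patients covered | Frequency | Duration |
|---|---|---|---|---|
| Section 2.5, regimen | Shenfu | treatment group | once daily | none |
| Section 2.5, regimen | nitroprusside | both groups | rate only, 3 μg/kg/min | none |
| Section 2.5, later sentence | none | all patients | once a week | none |
| Abstract, Methods | none (standard treatment) | both groups | none | 7 days |

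**Which pairs conflict**

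- Once daily and 7 days: compatible.
- Once a week and 7 days: no contradiction in themselves, since one injection fits into 7 days.
- Once daily and once a week: incompatible if both refer to Shenfu. The article describes no other trial injection, apart from the nitroprusside drip, that the weekly sentence could mean.

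The contradiction is therefore between two statements, both in section 2.5.

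**Size, under two assumptions**

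Assume (a) that the weekly sentence refers to Shenfu and (b) that the Abstract's 7 days are the Shenfu course.

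- Once daily: 7 days × 1 per day = 7 infusions; 7 × 40 mL = 280 mL of Shenfu.
- Once a week: 7 days ÷ 7 = 1 infusion; 1 × 40 mL = 40 mL of Shenfu.
- Ratio: 7 ÷ 1 = 7.

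If either assumption fails, this ratio does not apply.

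**The 72-hour assessment**

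Under a 7-day daily course, 72 hours from the first infusion is about day 3. From the last infusion it is about day 7 + 3 = day 10, after treatment has ended. Section 2.7 lists the 72-hour assessment before the end-of-treatment one. Read as a time sequence, this points to the start of a multi-day course, although the literal wording puts the 72 hours after the treatment. If there were only one infusion, 72 hours after it would already lie beyond the last dose, and the end of treatment would have no clear anchor.

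**Sample size (section 2.4)**

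The plan's own figure reproduces and contains no dosing term:

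- Per group: ((1.96 + 1.28) / 0.198)² × [0.723 × 0.277 + 0.921 × 0.079] = 267.77 × 0.27303 = 73.1, against 73 stated.
- With a 20% allowance: 2 × 73 / 0.8 = 182.5, against 182 stated.

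The frequency conflict changes neither figure.

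**The case against.** The strongest reply is that the text is not evenly balanced. The once-daily statement belongs to the only full drug specification, with product, volume, diluent, route and frequency. The 7-day period fits it, and the order of assessments in section 2.7 implies a course of several days. The weekly sentence names no drug, dose or duration, and it may be a slip for a one-week course. This stands as a reason not to call the exposure impossible to determine. It does not remove the conflict: the article nowhere says that the sentence is a slip, and a reader should not have to choose a dosing schedule by inference.

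A second reply is that the article condenses a fuller protocol. That would answer a missing detail, but this is a contradiction between two printed statements.

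Three stronger readings are tempting, and the document does not support them:

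- A reader might infer a three-way contradiction between daily, weekly and 7 days. Daily dosing and 7 days agree, and 7 days does not by itself exclude a weekly frequency.
- A reader might take the sevenfold difference as a fact. The weekly sentence names no drug, and the Abstract's 7 days refer to standard treatment, so the figure is conditional on both assumptions.
- A reader might infer that the assessment times are undefined, with day 10 as a live alternative. Under a 7-day daily course, the order in section 2.7 largely rules that out. The wording is loose, but this is a minor point.

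Unequal dosing within an arm, with dilution of the effect, would follow only if staff acted on different sentences. Nothing in the article shows that they would.

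**Conclusion.** The concern holds as an internal contradiction in section 2.5: Shenfu is once daily in the regimen, and a later sentence gives all patients a weekly injection without naming a drug. No other section reconciles the two. The Abstract's 7 days are compatible with daily dosing but do not settle the matter, because they are not tied to either study drug and are not repeated in the methods.

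The size is 7 Shenfu infusions against 1, provided that the weekly sentence means Shenfu and that the course is 7 days. Without those assumptions, no ratio can be stated. The wording of the 72-hour assessment is a secondary matter. The sample size, power and alpha are untouched.

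Because the conflict concerns the only treatment that differs between the arms, it should be corrected before the first patient is treated. This review takes no view on which schedule is right.

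**What to change.** 1. The sponsor should reconcile section 2.5 and the Abstract into one stated frequency and one stated duration for each drug in each arm, and place both in section 2.5.
2. Whichever statement does not match the reconciled schedule should be corrected or removed. If the weekly sentence stays in any form, it should name the drug and the arm.
3. As a minor consequential edit, section 2.7 should say whether the assessment described as "72 hours after the treatment and at the end of treatment" counts its 72 hours from the first or the last infusion.
4. If treatment has already begun, the schedule actually used should be documented.

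The cost is a wording correction. No recalculation is needed.
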